#### Descriptive analysis

Analysis will be done on the intent-to-treat sample population.

All patients’ characteristics at pre-test (V1), post-test (V2), and retention test (V3) will be described according to the randomization group. Qualitative variables will be described using frequency and percentages of each class. Quantitative variables will be described using median and quartiles.

#### Primary outcome measure analysis

The aim of the primary outcome analysis will be to compare the functional motor capacity of the UL (WMFT) in the intervention group comparatively to the placebo group at V3. The normality of the data from the WMFT will be analysed by the Shapiro-Wilk test. The variance homogeneity will be assessed using the Bartlett test. If the normality is respected, a parametric Student *t*-test will be performed for mean comparisons. If the distribution of the data is not normal, a non-parametric Wilcoxon signed-rank test will be used.

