#### Randomization

The Capture System software (Ennov Clinical, module randomization, Paris, France) will be set up by the randomization administrator, from the Innovation and Research Department of the Hospital, to give a blinding code to each patient. A centralized randomization will be performed using the Capture System software (Ennov Clinical, module randomization, Paris, France). A minimization algorithm will assure the balance of groups regarding PRM centres (CHU Montpellier or Nimes) and stroke severity (FM-UE score lower or higher than 40 [72]); see “Blinding of group and stimulation protocols” section for more details. For each inclusion, another hospital department, the clinical investigation centre, will use the software to allocate the right protocol.

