### Statistical analysis

#### Sample size

Allman et al. [1] reported that compared to sham, real anodal tDCS (1 mA, conventional montage, ipsilesional motor cortex) combined with 9 days of UL rehabilitation in chronic stroke patients had a moderate effect size *d* = 0.4 on the WMFT at 3 months after the intervention. In the meta-analysis of Chhatbar et al. [16], UL motor recovery (FM-UE) in a chronic stroke population was superior in the group receiving a real tDCS (in comparison to sham) with higher current density and smaller electrode size (large effect size *g* = 1.23). Because we will use anodal HD-tDCS with a higher current density (2 mA) and longer rehabilitation dose (13 days) in chronic stroke patients, we estimate that our protocol should have an effect size of *d* = 0.8 on the WMFT at 3 months. Using an alpha bilateral risk of 5% and a power of 80%, 26 patients per group are needed for analysis. If we count a loss of 10% of the patients, we will have to recruit 58 patients (*n* = 29 per group).

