#### Statistical method

Statistical analysis will be performed using the latest version of the free R software. A *p*-value of 0.05 will be considered significant for all analyses. All outcome measures will be assessed at V1, V2, and V3. The primary outcome will be the difference between both groups (*intervention, placebo*) at V3 on the WMFT. The secondary outcomes will be the changes between V1 and V2 (learning) and between V2 and V3 (retention) for both groups.

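### Bartlett's test has no consequence in the primary analysis, and Student's pooled t-test stands in the normal branch even if equal variances are rejected; Welch's test would close this small gap almost free

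*Protocol article*

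**What the plan says.** The section Primary outcome measure analysis announces two checks on the WMFT data: a Shapiro-Wilk test of normality and a variance check, "The variance homogeneity will be assessed using the Bartlett test". It then gives two branches. The first reads "If the normality is respected, a parametric Student" t-test for the comparison of means. The second, for non-normal data, is a Wilcoxon test. Both conditions concern normality only. The Bartlett result is not used again, and the article names no unequal-variance test.

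The level is fixed under Statistical method: "A *p*-value of 0.05 will be considered significant for all analyses". The sample size section works to the same two-sided level: "Using an alpha bilateral risk of 5% and a power of 80%, 26 patients per group are needed for analysis". It then adds 10% for loss and recruits 29 per arm. Allocation is by minimisation on centre and FM-UE severity. The primary comparison is "The primary outcome will be the difference between both groups (*intervention, placebo*) at V3 on the WMFT".

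**The concern.** Student's t-test pools the two variances. When the arms are equal in size, the pooled standard error is right on average whatever the two variances are. When the arms differ in size and the variances also differ, it is wrong in a known direction: too small if the smaller arm is the more variable, too large if the larger arm is. The first makes the test liberal, the second conservative.

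The plan considers variance homogeneity worth testing, yet read as written it keeps the test that relies on homogeneity when the check fails. Neither minimisation nor an expected 10% loss guarantees equal arms among those analysed at V3. At stake is the calibration of the primary p-value, and of any interval reported with it, under particular combinations of attrition and spread.

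**Working it through.** **Inputs from the article.** Two-sided alpha 5%, power 80%, d = 0.8, 26 analysed per arm, 10% loss, 29 recruited per arm.

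**Assumed inputs.** SD ratio between arms at V3 from 1 to 3 (no SD is given), and the analysed arm sizes shown below.

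**1. The plan's own figure.** The noncentral-t calculation at d = 0.8 gives power of 79.1% with 25 per arm and 80.7% with 26, so 26 is correct. 26 / 0.9 = 28.9, hence 29 per arm and 58 in total. Both figures reproduce.

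**2. Mechanism.** Put SD r in arm 1 and SD 1 in arm 2.

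- Expected pooled variance: s² = [(n1 − 1)r² + (n2 − 1)] / (n1 + n2 − 2)
- Squared standard error used by Student's test: s²(1/n1 + 1/n2)
- True variance of the difference in means: r²/n1 + 1/n2

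With r = 2:

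- 26 v 26: s² = 2.50; used 0.1923, true 0.1923; ratio 1.00.
- 24 (SD 2) v 28 (SD 1): s² = (23×4 + 27)/50 = 2.38; used 0.1842, true 4/24 + 1/28 = 0.2024; ratio 0.91. The standard error is about 4.6% too small, since √0.91 = 0.954.
- 28 (SD 2) v 24 (SD 1): s² = (27×4 + 23)/50 = 2.62; used 0.2027, true 4/28 + 1/24 = 0.1845; ratio 1.10. The standard error is about 4.8% too large, since √1.0987 = 1.048.

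**3. Type I error of Student's test.** Nominal 5%, normal data, equal means, 400,000 simulated trials per setting:

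| Analysed arms | More variable arm | SD ratio 1.5 | SD ratio 2 | SD ratio 3 |
|---|---|---|---|---|
| 26 v 26 | either | 5.1% | 5.2% | 5.3% |
| 28 v 24 | smaller | 5.8% | 6.3% | 7.0% |
| 28 v 24 | larger | 4.5% | 4.2% | 3.9% |
| 29 v 23 | smaller | 6.1% | 6.9% | 7.8% |
| 29 v 23 | larger | 4.2% | 3.7% | 3.5% |

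Welch's test lies between 4.9% and 5.1% in every cell.

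**4. How often the arms would be that unequal.** If each of 29 patients per arm is lost independently with probability 0.10, the analysed arms differ by 4 or more in about 12% of trials and by 6 or more in about 1.6%. Averaged over that loss distribution, Student's type I error is about 5.1% at SD ratio 1.5, 5.2% at 2 and 5.4% at 3.

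**5. Does the normality check rescue it?** The whole two-stage rule was simulated (Shapiro-Wilk in each arm, then a t-test, or a rank-sum test as a stand-in for the non-normal branch; 20,000 runs). At 23 v 29 with SD ratio 2 and the smaller arm more variable, the overall error is 7.1% with Student's test and 5.2% with Welch's. The gate does not remove the drift.

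**6. Would acting on Bartlett's test be enough?** At 26 per arm it rejects in about 51% of trials at SD ratio 1.5 and 92% at SD ratio 2. As a gate it would miss half the cases at the lower ratio.

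**7. Price of Welch's test.** At d = 0.8 with equal variances, simulated power is 80.80% against 80.84% for Student's test at 26 v 26. With 23 in the arm listed first and 29 in the other it is 80.06% against 80.23%.

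**The case against.** The strongest objection concerns the mechanism. A reader might infer that the primary test fails to hold its 5% level, particularly because stimulation may help some patients and not others and so spread out the active arm. The article does not support that. If stimulation does nothing, randomised arms share one distribution, the variances are equal and Student's test holds its level. If it helps some patients and harms none, the means differ, and rejecting is not a type I error. The rates in the table need equal means with unequal spread, for example benefit and harm cancelling, and nothing in the article suggests this. Under a real effect, what remains is the calibration of the standard error and of any interval. The statistical sections do not mention a confidence interval, so even that is a consequence for reporting.

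The other objections are about size and scope. The SD ratios have no source in the article. Large imbalance is uncommon with 1:1 allocation and 10% loss: 29 v 23 would need all six losses in one arm. Student's test also applies only in the normal branch, and a WMFT time score capped at 120 s may never reach it. All of this stands and limits the point to a small one. Losses that differ systematically by arm could make imbalance more common, but the article gives no figure for that.

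It can also be said that the response to a Bartlett rejection is detail for the analysis plan. That carries less weight. The article does set out the decision rule for the primary test, and the rule contains a step that leads nowhere.

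**Conclusion.** The point holds in a limited form. As written, the variance check is inert and Student's test is used in the normal branch whatever that check shows. With the planned near-equal arms the cost is negligible, about 5.1% to 5.3% at 26 v 26. The drift is roughly 4% to 6% at 28 v 24 with SD ratios of 1.5 to 2, and about 3.7% or 6.9% at 29 v 23 with SD ratio 2. Those figures rest on assumed SD ratios, equal means, normal data and attrition that happens to fall unevenly. They do not support the statement that the primary test fails to hold its 5% level; averaged over independent 10% loss, the excess is at most about 0.4 point even at SD ratio 3. The sample size is unaffected. The reason to change the text is that a better-behaved test costs practically nothing, and a check without a stated consequence invites a choice of test after the data are seen.

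**What to change.** Delete the Bartlett step and name Welch's unequal-variance t-test as the parametric comparison in the normal branch, whatever the observed variances. Do not turn Bartlett's test into a gate, because it misses about half the cases at SD ratio 1.5.

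The change is one sentence. It costs about 0.1 percentage point of power at 26 per arm with equal variances and under 0.2 point at 29 v 23; 26 analysed and 29 recruited per arm stand. R, the software named in the article, uses Welch's version by default in its two-sample t-test function, so the change also brings the text into line with what a default call would run.

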### Description of testing visits and outcome measures

Table 2 presents the timing of the testing visits and outcome assessment measures. The baseline assessment (pre-test) visit (V1) will take place on the first day of the 3-week in-patient hospital rehabilitation stay. A specialist trained therapist will run the clinical assessments (WMFT, FM-UE, Box and Block Test (BBT), Bell’s test, MMSE, Barthel Index (BI); more details in the “Clinical data and outcome measures” section). Patients UL kinematics and motor cortical region activation will then be evaluated by one of the investigators on three functional motor tasks: a seated reaching task (Proximal Arm Non-Use, PANU), a circular steering task, and the Ladybug game of the Armeo VRT platform used for rehabilitation. The next day (day 2), patients will start the standard in-patient stroke rehabilitation program that will last for 13 complete days (excluding weekends) over 3 weeks.

**Table 2 Tab2:** Study testing visits (V1-3) and outcome assessments

Outcome measures	Inclusion visit	Pre-test (V1)	Post-test (V2)	Retention test (V3, 3 months after V2)
Mini Mental State Examination	X			
Boston diagnostic aphasia examination	X			
Bell’s test	X			
Wolf Motor Function Test		X	X	X
Fugl-Meyer Upper Extremity		X	X	X
Box and Block Test		X	X	X
Barthel Index		X	X	X
Actimetry		X	X	X
Proximal Arm Non-Use (PANU)^a^		X	X	X
Reaching task (Kinematics and EEG/fNIRS)		X	X	X
Circular steering task (Kinematics and EEG/fNIRS)		X	X	X
Lady bug test (Kinematics and EEG/fNIRS)		X	X	X

^a^Proximal Arm Non-Use will be assessed during the reaching task

*EEG* Electroencephalography, *fNIRS* Functional near-infrared spectroscopy

The post-test visit (V2) will take place the last day of the 3 weeks (day 19); the post-test will be identical to the pre-test. The 3-month visit (V3) will take place 3 months after the end of the rehabilitation program (day 19) for a retention test and will be identical to the pre- (V1) and post- (V2) tests.

Patients will be given actimetry bracelets to be worn on each UL to measure UL activity for 7 days before V1, for 7 days after V2, and for 7 days after V3.

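### The primary WMFT comparison at V3 is unadjusted and its test is picked by a normality pre-test; it is valid, but it forgoes the precision available from baseline WMFT and the minimisation factors

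*Protocol article*

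**What the plan says.** Under *Statistical method* and *Primary outcome measure analysis*, the protocol article defines the primary comparison as intervention against placebo on the WMFT at V3. Shapiro-Wilk is applied to the WMFT data. "If the normality is respected, a parametric Student" t-test compares means; if not, a Wilcoxon signed-rank test is used. The same paragraph adds: "The variance homogeneity will be assessed using the Bartlett test". It does not say what follows from the result.

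No covariate is named on either branch. Yet Table 2 schedules the "Wolf Motor Function Test" at V1, V2 and V3, and the *Randomization* section states: "A minimization algorithm will assure the balance of groups regarding PRM centres (CHU Montpellier or Nimes) and stroke severity", with severity split at an FM-UE score of 40.

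The *Sample size* section assumes d = "0.8 on the WMFT at 3 months" and concludes: "Using an alpha bilateral risk of 5% and a power of 80%, 26 patients per group are needed for analysis". The effect it cites from the earlier tDCS trial is smaller, d = "0.4 on the WMFT at 3 months after the intervention".

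Two other places bear on the point. The WMFT section under *Primary outcome measure* gives the clinically important difference for between-group change scores. Linear mixed models over all three visits appear only under *Other/exploratory outcome measures analysis*.

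**The concern.** Eligibility starts at FM-UE 15 with no stated ceiling, and patients are more than 3 months after stroke. A patient's V1 WMFT is therefore likely to predict the V3 value. A V3-only comparison leaves that predictable variation in the error term. Centre and FM-UE were thought important enough to drive allocation. If they are prognostic, leaving them out of the analysis tends to make the t-test conservative.

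The normality gate is a separate weakness. The trial data decide whether means or ranks are compared, so what the primary test addresses is not settled in advance. The rank branch also names a test for paired data, although the two arms are independent groups. The Bartlett result triggers nothing.

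At stake is the chance of detecting a real effect with 58 patients, above all if the true effect is nearer the cited 0.4 than the planned 0.8.

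**Working it through.** **Inputs from the documents** (*Sample size*): two-sided alpha 0.05; power 80%; d = 0.8 planned and d = 0.4 cited; 26 evaluable per arm; 10% loss.

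**Assumed inputs:** V1-V3 correlation ρ of 0.5, 0.7 or 0.8 (no value is given); d scaled by the SD of WMFT at V3; residuals approximately normal.

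**1. The plan's own figure.** A two-sample t-test (noncentral t) at d = 0.8 needs 25.5, so 26 per arm; power at 26 is 80.7%. Allowing for loss, 26 / 0.90 = 28.9, so 29 per arm and 58 in total. The stated numbers reproduce, and they belong to the unadjusted comparison.

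**2. Adjusting for V1 WMFT.** ANCOVA multiplies the residual variance by 1 − ρ², so the effective effect size is d / √(1 − ρ²). Power below is for 26 per arm, with one degree of freedom charged for the covariate.

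| ρ | 1 − ρ² | Effective d (from 0.8) | Power, d = 0.8 | Effective d (from 0.4) | Power, d = 0.4 |
|---|---|---|---|---|---|
| unadjusted | 1 | 0.80 | 80.7% | 0.40 | 29.3% |
| 0.5 | 0.75 | 0.92 | 89.8% | 0.46 | 36.6% |
| 0.7 | 0.51 | 1.12 | 97.5% | 0.56 | 50.0% |
| 0.8 | 0.36 | 1.33 | 99.7% | 0.67 | 64.5% |

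Without the charge for the covariate, the d = 0.4 figures are 37.2%, 50.8% and 65.4%. The effect detectable with 80% power falls from 0.79 to 0.79 × √0.75 = 0.69, 0.79 × √0.51 = 0.57 and 0.79 × √0.36 = 0.48.

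**3. Adding the minimisation factors.** Two further covariates cost at most about 1.3 points of power for ρ of 0.5 or more (at d = 0.8, ρ = 0.5: 89.8% to 88.5%), before counting any variance they explain.

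**4. The gate, by simulation** (3,000 runs per scenario, 26 per arm, with a rank-sum test standing in for the signed-rank test, which does not apply to independent groups). With normal data the two-stage procedure had type I error of 5.2% and 5.9% in two scenarios and power of about 80% at d = 0.8. With lognormal data the normality check almost never passed; type I error was 4.9% to 5.1%. The power difference therefore comes from omitting baseline, not from the gate.

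**5. Where adjustment does not help.** In the lognormal simulation (d = 0.8 on the log scale), raw-scale ANCOVA had 69% power at ρ = 0.5 against 78% for the rank test, and 91% against 78% at ρ = 0.8. The scale has to be chosen along with the model.

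**The case against.** The strongest reply is that nothing here is invalid. An unadjusted comparison of randomised groups is legitimate, and at d = 0.8 it delivers the power that the plan asked for. That stands, and it makes this an efficiency recommendation.

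The size of the gain also rests on a correlation that the documents do not give, and on reading d as scaled by the V3 SD, which *Sample size* does not state. If d were scaled by the SD of change, the effect in V3 SD units would be d × √(2(1 − ρ)). At d = 0.4 and ρ = 0.8 that is 0.4 × √0.4 = 0.25, with power of about 15% unadjusted and 31% adjusted. Adjustment still helps, but the table above does not apply. Skewed, capped times weaken it further, as step 5 shows.

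A reader might infer three stronger things that the documents do not support:

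- **That the gate inflates false positives.** The simulated error stays near 5%.
- **That a chance baseline gap could pass for an effect.** Chance imbalance is already within the 5% error rate of a randomised comparison. Imbalance odds worked out for simple randomisation do not describe this minimised design.
- **That the rank branch can give no estimate in WMFT units.** A Hodges-Lehmann shift with a confidence interval is available; the article merely names no estimate.

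The Bartlett point is minor, since the t-test with equal arms is robust to unequal variances.

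The absence of a visible SAP does not answer the point. The article itself names a specific unadjusted test, so an adjusted analysis in the SAP would contradict it.

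**Conclusion.** The point holds as forgone efficiency plus a data-dependent choice of test. The trial keeps its stated 80% power at d = 0.8 under the V3-SD reading, and type I error is not at issue.

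Under the assumptions listed, adjusting for V1 WMFT adds about 9 to 19 points of power at d = 0.8 and about 7 to 35 points at d = 0.4, for ρ from 0.5 to 0.8. The gain is modest at 0.5 and large from 0.7 upward. A high correlation is plausible in this population but undocumented, so it would go too far to say that the plan loses much of its power.

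Two defects in the wording stand without any assumption. The signed-rank test does not fit two independent groups. The change-score wording of the clinically important difference does not match the V3-only comparison. The change should be made, but the trial is not invalid without it.

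**What to change.** Replace the Shapiro-Wilk and Bartlett gate in *Primary outcome measure analysis* with one pre-specified linear model: V3 WMFT on group, V1 WMFT, centre and FM-UE (stratum or continuous). Report the adjusted group difference with its 95% confidence interval, using heteroscedasticity-robust standard errors.

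If the time score is primary, analyse it on the log scale and say how the result, a ratio of times, will be set against a clinically important difference given in seconds.

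Name a rank-based sensitivity analysis suited to independent groups (rank-sum or rank ANCOVA) in place of the signed-rank test.

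Reconcile the change-score wording in the WMFT section with the V3 comparison. With V1 WMFT in a linear model on the raw scale, the group coefficient is the same whether the response is V3 or change from V1, so one sentence can settle this.

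The cost is protocol and SAP wording and a few degrees of freedom. Every covariate is already collected, and the sample size can stay at 58.

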### Study design

Figure 1 shows a flow diagram of the study design. The ReArm project is a quadruple-blinded, randomized, sham-controlled, bi-centre, two-arm parallel, and interventional study. All patients will undergo 3 weeks of a standard in-patient stroke rehabilitation program (see details in the next section) and will thereafter be followed over a period of 3 months. One group (intervention) will receive 3 weeks rehabilitation consisting of standardized conventional therapy rehabilitation and combined VRT and anodal HD-tDCS. The second group (placebo) will receive standardized conventional therapy rehabilitation and combined VRT and sham HD-tDCS.

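### The non-normal branch of the primary analysis names the Wilcoxon signed-rank test, a paired test, for a comparison of two independent randomised groups

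*Protocol article*

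**What the plan says.** The Study design section of the protocol article describes a "randomized, sham-controlled, bi-centre, two-arm parallel, and interventional study". Under Randomization, "A minimization algorithm will assure the balance of groups regarding PRM centres" and regarding stroke severity; this balances the groups without matching individual patients.

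The Statistical method section sets the contrast: "The primary outcome will be the difference between both groups" at V3 on the WMFT. The Primary outcome measure analysis section repeats it as a comparison of functional motor capacity "in the intervention group comparatively to the placebo group at V3".

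That section then makes the choice of test depend on the data: "The normality of the data from the WMFT will be analysed by the Shapiro-Wilk test", and a Bartlett test is used for variance homogeneity. If normality holds, a Student t-test compares means. Otherwise: "If the distribution of the data is not normal, a non-parametric Wilcoxon signed-rank test will be used".

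No section names a rank-sum or Mann-Whitney test, and none defines a pairing of intervention with placebo patients.

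**The concern.** The signed-rank test ranks within-pair differences, or deviations of one sample from a fixed value. A contrast between two unmatched groups at one visit provides neither, so this branch of the primary analysis has no defined result.

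The stake is pre-specification. If normality is rejected, the analyst must either invent a pairing or replace the named primary test after the data are in. The first gives a p-value that another analyst could not reproduce. The second is a post hoc change to the primary analysis, even if made for good reasons. A separate analysis plan might give more detail, but this is not a gap left for that document: the article names a test, and the test does not fit the design.

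**Working it through.** **1. Does the plan's own sample size assume independent groups?** Inputs from the Sample size section: d = 0.8, two-sided alpha 5%, power 80%, 10% loss.

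- Normal approximation: 2 × (1.96 + 0.8416)² / 0.8² = 2 × 7.849 / 0.64 = 24.5, so 25 per group.
- Independent two-sample t-test (noncentral t): 25.52, so 26 per group; power at 26 is 80.7%.
- Allowance for loss: 26 / 0.9 = 28.9, so 29 per group and 58 in total.

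The stated 26 and 58 are reproduced exactly. The sizing treats the groups as unpaired, and so does the Bartlett test and t-test branch.

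**2. Can the named test be run?** It needs equal numbers. Assume each of 29 patients per arm is lost independently with probability 0.10. The chance that the two completer counts differ is 1 − Σₖ [C(29,k) 0.9ᵏ 0.1²⁹⁻ᵏ]² = 0.823, or about 82%. A trial call with 26 and 25 values returned an error.

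**3. What happens if the arms are equal?** Data were simulated as normal with SD 1 and 26 per arm.

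- *Dependence on row order.* Each data set was paired at random 60 times. At d = 0.8 at least one ordering changed the significance verdict in about 30-38% of data sets across separate runs. The typical 5-95% range of p within a data set was about 0.003 to 0.03, so the verdict changes mainly in data sets near the threshold.
- *One example.* In a single data set the signed-rank p ran from 0.16 to 1.00 over 2,000 pairings, while the rank-sum test gave one value, 0.60.
- *Long-run behaviour under random pairing* (20,000 data sets):

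| Test | Rejection rate, d = 0 | Rejection rate, d = 0.8 |
|---|---|---|
| Signed-rank, arbitrary pairs | 5.1% | 77.4% |
| Rank-sum | 5.0% | 78.9% |
| t-test | 5.1% | 81.1% |

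The error rate is therefore sound on average. The fault is that a given data set has no single answer.

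**4. How often would this branch apply?** The protocol gives no WMFT distribution. Its Primary outcome measure section lists four scores, including a median time (0-120 s) and a summed functional score (0-75), and the statistical sections say only WMFT. Everything here is therefore assumed. Shapiro-Wilk was applied at 5% in each arm of 26, and the fallback counted as triggered if either arm rejected.

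| Assumed distribution | Fallback triggered |
|---|---|
| Lognormal time, median 5 s, cap 120 s, log-SD 0.3 | about 52-55% |
| Same, log-SD 0.5 | about 88% |
| Same, log-SD 0.7 | about 98% |
| Same, log-SD 1.0 to 1.3 | over 99% |
| Roughly normal 0-75 score (mean/SD 40/12, 45/15, 55/12) | about 7-13% |
| Exactly normal data | about 10% |

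**The case against.** The strongest reply is that this is a naming slip. The stated aim, the t-test branch, the Bartlett test and the sample size are all unpaired, so a competent analyst would read rank-sum. With unequal arms the software would refuse the paired test, so the slip would probably surface before any result was reported. That is likely correct, and it limits the practical harm. It does not remove the point, because a pre-specified primary test should be executable as worded, and correcting it after data collection looks like a choice made on the data.

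The documents do not support three stronger readings that a reader might infer:

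- *That the faulty branch will probably produce the primary result.* The 120 s cap and the plan to describe quantitative variables by median and quartiles point towards skewed times. But no distribution is given, the primary WMFT score is not identified, and a roughly normal functional score would seldom trigger the fallback.
- *That false positives would rise.* Random pairing keeps type I error near 5%.
- *That the plan intends a within-arm test of change from V1 to V3.* Such a test would not measure the treatment effect, but the section states a between-group aim at V3 and proposes no such test.

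**Conclusion.** The point holds for one branch of the primary analysis. The named fallback is a paired test, the contrast is between independent groups, and nothing elsewhere in the article corrects it. The design and the wording alone establish this; no distributional assumption is needed.

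The size of the consequence does rest on assumptions. The 82% chance of unequal arms assumes independent 10% loss in each arm. The 30-38% order-dependence assumes equal arms of 26, normal data, d = 0.8 and 60 orderings per data set. The frequency of the branch runs from about 7% to 100% according to the score and its distribution. The t-test branch stands as written, so it would be wrong to conclude that the primary analysis as a whole is invalid.

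**What to change.** In the Primary outcome measure analysis section, replace the signed-rank test with the two-sample Wilcoxon rank-sum (Mann-Whitney) test for independent groups. Optionally, report with it a Hodges-Lehmann difference and 95% CI.

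The cost is one line of wording, made before unblinding, and no new data. The effect on power is small: with normal data, 26 per arm and d = 0.8, the rank-sum test has 78.9% simulated power. At its normal-theory efficiency of 3/π = 0.955, full 80% power would take 25.52 / 0.955 = 26.7, so 27 analysed per arm. After 10% loss that is 27 / 0.9 = 30 recruited per arm, or 60 instead of 58. Correcting the test name does not depend on making that change.
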